### Outcome assessment

#### Primary outcome measures

The primary outcome is objectively measured PA at 6 weeks (t3) and 6 months (t4) after PR. Baseline measurement of PA is conducted 2 weeks before the inpatient PR begins (T0). PA is measured on seven consecutive days with a three-axial accelerometer PA monitor (Actigraph wGT3X-BT). This activity monitor is the one of the most accurate devices for COPD patients and is explicitly recommended as a valid tool to measure PA in this clinical population [21–23].

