### Hypothesis

#### Primary hypothesis

In individuals with COPD, inpatient PR (= standard care) plus a pedometer-based BCI will result in a significantly higher level of PA 6 weeks and 6 months after rehabilitation compared to standard care plus a short revision of patient education.

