### Sample size and power calculation

A consecutive sample of 351 PR patients is needed. Pedometer-based interventions are among the most effective intervention components to promote PA in everyday life [8]. Meta-analysis has shown, in comparison to control groups, an average mean effect size of 0.68 on PA which represents an increase of 2000 steps per day [12]. The long-term effect on PA of standard inpatient PR in people with COPD is assumed to be small [16]. In comparison to standard PR we expect a small effect (*d* = 0.3) at t4. The power calculation (by means of software G*Power 3.0) with respect to the primary target (analysis of covariance to t4, mean effect size of *d* = 0.3, an alpha error level of 5%, and statistical power of 80%) results in a required sample of at least 351 subjects with complete data. In a preliminary pilot study, a generally high willingness to participate of 96% was recorded. A dropout of 30% from baseline measurement t0 to t4 is estimated based on the pilot study. With this dropout rate, the recruitment of a total of 502 subjects (251 subjects per group) is necessary. The study sample size is adequate for the determination of PA predictors after rehabilitation and with a weekly average of 12 subjects and a conservative recruitment rate of 66%, the study aims should be reached within the recruiting period of 15 months.

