### Data analysis

#### Statistical analysis and evaluation

Regarding the primary objective, a baseline-controlled comparison (covariance) of the post values between the initial assigned control and the intervention treatment group (intention-to-treat analysis) at the time points t3 and t4 will be provided for statistical analysis.

For the secondary objective a cluster-based analysis method will be used for longitudinal records (e.g., linking of clusters after removal of a residue (LICUR); [25]). In this case the analysis creates separate clusters for each measurement using the comprehensive assessment battery for t1 and t2 and especially using the accelerometer PA data for t0, t3 and t4. The second step of the cluster-based analysis links separately created clusters in a longitudinal way.

A strategy for dealing with missing data will be developed in cooperation with a biostatistician. If adequate and realistic, missing data will be substituted by multiple imputation.

The processing of PA monitoring data as the primary outcome will be conducted as follows: the PA monitor will be worn for seven consecutive days with a minimum of four valid days inclusive of a weekend day [26–28]. A day is considered valid if subjects wear the device for ten or more waking hours [26–28], where non-wear time is set at 60 min of zero counts of which up to 2 min may be within the 0–100 count range [28, 29]. Current research points towards avoiding the use of direct monitor outputs such as energy expenditure estimations due to issues with reliability [21, 30]. Consensus points towards the use of both sedentary and moderate to vigorous physical activity (MVPA) cutoff points where sedentary activity is seen as 0 to > 100 counts per min [27, 29, 31, 32] and MVPA as > 1952 counts per min [29]. While the use of the LFE filter to calculate steps is not recommended, it may be applicable during data analysis of cutoff points for older adults [33, 34]. Future work on defining cutoff points in clinical populations will be considered.

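### PA at 6 weeks and at 6 months are both primary in the hypothesis, outcome and analysis sections, but the sample size treats 6 months alone as the primary target

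*Protocol article*

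**What the plan says.** Three sections of the protocol article put both follow-up times in the primary claim:

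- Primary outcome measures: "The primary outcome is objectively measured PA at 6 weeks (t3) and 6 months (t4) after PR".
- Primary hypothesis: the intervention "will result in a significantly higher level of PA 6 weeks and 6 months after rehabilitation".
- Statistical analysis and evaluation: for the primary objective, a baseline-adjusted intention-to-treat comparison "at the time points t3 and t4 will be provided for statistical analysis".

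One section names a single time. Sample size and power calculation computes power "with respect to the primary target (analysis of covariance to t4", after stating "In comparison to standard PR we expect a small effect (*d* = 0.3) at t4". The 5% alpha and 80% power appear only in that calculation, which "results in a required sample of at least 351 subjects with complete data". With 30% dropout this becomes 502 recruited, 251 per group. No effect size is given for t3, and the article states no ranking of the two times.

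**The concern.** Two different trials can be read from this text. One has a single primary endpoint at 6 months. The other has a primary hypothesis covering 6 weeks and 6 months together. The sample size belongs to the first; the hypothesis, outcome definition and analysis describe the second.

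The difference could decide how the trial is reported. The Background and Discussion treat the 6-week result as initiation of an active lifestyle and the 6-month result as its maintenance. The Background also says that rehabilitation programs often fail to raise activity in the long term. A positive t3 with a null t4 is therefore a realistic result. Under the sample size section it misses the primary target. Under the hypothesis read as a conjunction it also fails. Under the outcome definition, someone could say that one of two primary time points was met. The choice should be fixed before the data are seen.

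**Working it through.** **Inputs.** From Sample size and power calculation: d = 0.3 at t4, alpha 5%, power 80%, 351 completers, 30% dropout, equal groups. Not in the document and assumed here: the correlation ρ between the t3 and t4 test statistics (0 to 0.9) and the effect at t3 (d = 0.3, 0.4 or 0.5). Sidedness is not stated; two-sided is inferred because it reproduces 351, whereas a one-sided test gives 276.

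**Step 1: reproduce the plan's figure.** For an analysis of covariance with two groups and one covariate, f = d/2 = 0.15 and the noncentrality is f² × N = 0.0225 × 351 = 7.90. The noncentral F test at 5% gives power 0.800 at N = 351, the smallest N that reaches 80%. The normal approximation agrees: 2 × (1.960 + 0.842)² / 0.3² = 174.4, so 175 per group and 350 in total. Dropout: 351 / 0.70 = 501.4, rounded up to 502. Both stated figures hold for t4 alone.

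**Step 2: power at one time point.** The expected test statistic is d × √N / 2 = 0.3 × √351 / 2 = 2.810. Power is Φ(2.810 − 1.960) = Φ(0.850) = 0.802.

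**Step 3: the two decision rules.** The two statistics are taken as bivariate normal with correlation ρ.

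- Both required at 5% each: joint power = P(both exceed 1.960). At ρ = 0 with d = 0.3 twice this is 0.802² = 0.644. With d = 0.4 at t3, the t3 power is Φ(0.4 × √351 / 2 − 1.960) = Φ(1.787) = 0.963, and 0.802 × 0.963 = 0.773.
- Either suffices at 5% each: the family-wise error at ρ = 0 is 1 − 0.95² = 0.0975. The chance of at least one success is 2 × 0.802 − joint power.

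| ρ (assumed) | Either: family-wise error | Either: at least one success, d = 0.3 at both | Both: d at t3 = 0.3 | Both: d at t3 = 0.4 | Both: d at t3 = 0.5 | Completers for 80% on both, d = 0.3 at both |
|---|---|---|---|---|---|---|
| 0 | 9.75% | 96% | 64% | 77% | 80% | 459 |
| 0.5 | 9.1% | 91% | 69% | 79% | 80% | 435 |
| 0.8 | 7.8% | 87% | 73% | 80% | 80% | 408 |
| 0.9 | 7.0% | 85% | 75% | 80% | 80% | 392 |

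Dividing the last column by 0.70 gives 656, 622, 583 and 560 recruited.

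**Step 4: rules that control the error.** Splitting alpha to 2.5% at each time gives about 71% power per time point at N = 351. Restoring 80% takes 425 completers, and 425 / 0.70 rounds up to 608 recruited. Testing t4 first at 5%, and t3 at 5% only after a significant t4, keeps the family-wise error at 5% and power at t4 at 80% with 351 and 502.

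**The case against.** The strongest reply is that nothing stated is numerically wrong. The 80% is tied explicitly to t4, is never offered as joint power, and reproduces. The primary hypothesis joins the two times with a literal and; read that way, each test at 5% needs no correction, and a positive t3 with a null t4 simply fails. The article nowhere says that one time point is enough. Since this is a condensed article, a multiplicity rule may sit in an analysis plan that is not shown.

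All of this stands, and it rules out several stronger readings that a reader might infer:

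- That each time point is tested at 5%. The 5% appears only in the t4 power calculation.
- That error rate and power both fail. Under unadjusted testing no single rule does both: the either rule inflates error but leaves at least 85% chance of a success at d = 0.3, and the both rule costs power but holds the error.
- That the confirmatory claim has no defined error rate. The conjunctive reading controls it.
- That joint power is necessarily near 70%. This depends on an effect of only 0.3 at t3, which the article does not state. The dropout is also counted through to t4, so more than 351 may have data at t3.
- That the lack of a multiplicity rule is itself a fault. An article may leave that to the analysis plan.

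The reply does not remove the contradiction between sections. A separate analysis plan could add a rule, but it would not make the hypothesis, outcome and analysis sections agree with a sample size section that names t4 alone as the primary target.

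**Conclusion.** The concern holds as an internal inconsistency: both times are primary in three sections, and t4 alone is the primary target in the fourth. The 351 and 502 figures are right for t4 only.

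The consequence depends on which rule was meant. If both are required, type I error is at or below 5% and the chance of meeting the primary hypothesis with 351 completers is about 64–75% for equal effects of 0.3, rising to 77–80% if the t3 effect is 0.4 or more. If either suffices at an unadjusted 5% each, the family-wise error is about 7–10% and power is not short. These ranges rest on an assumed correlation of 0 to 0.9 and on assumed t3 effects.

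This should be fixed before analysis. It does not invalidate the design or the sample size.

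**What to change.** Reconcile the four sections before any comparison by group. The option that matches the sample size section is to name PA at t4 as the single primary endpoint, tested two-sided at 5%, with t3 next in a fixed sequence and tested at 5% only if t4 is significant. This needs no extra patients: 351 and 502 stand. The price is that t3 cannot be claimed as confirmatory if t4 fails, and the primary hypothesis becomes narrower.

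If the sponsor wants the conjunction, say that both time points must be significant at 5% each, state that the 80% applies to t4 only, and give the joint power as a range over the assumed t3 effect and correlation. An either-one rule with alpha split is less practical, since it needs 425 completers (608 recruited) for 80% at each time and recruitment was due to end in September 2017.

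Whichever is chosen, this is a change to the definition of the primary endpoint made late in recruitment. It should be dated and entered in the registry, as the Trial registration section commits to do for all protocol modifications.

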#### Secondary outcome measures

Secondary outcome measures will assess central psychological and physical functional determinants of long-term health-promoting PA applicable to patients following PR. As defined by the PARC model [24] the following characteristics will be collected: physical motor functions and consequences of health problems in functioning (physical function and disease-related impairments in activities and participation), motivation and volition, sports-related goals and motives, stage of behavior change, as well as characteristics of health and wellbeing. Data will be entered and stored at the Erlangen Study Center. Outcomes of the study and time frames for their collection are shown in Fig. 2.

### Data analysis

#### Statistical analysis and evaluation

Regarding the primary objective, a baseline-controlled comparison (covariance) of the post values between the initial assigned control and the intervention treatment group (intention-to-treat analysis) at the time points t3 and t4 will be provided for statistical analysis.

For the secondary objective a cluster-based analysis method will be used for longitudinal records (e.g., linking of clusters after removal of a residue (LICUR); [25]). In this case the analysis creates separate clusters for each measurement using the comprehensive assessment battery for t1 and t2 and especially using the accelerometer PA data for t0, t3 and t4. The second step of the cluster-based analysis links separately created clusters in a longitudinal way.

A strategy for dealing with missing data will be developed in cooperation with a biostatistician. If adequate and realistic, missing data will be substituted by multiple imputation.

The processing of PA monitoring data as the primary outcome will be conducted as follows: the PA monitor will be worn for seven consecutive days with a minimum of four valid days inclusive of a weekend day [26–28]. A day is considered valid if subjects wear the device for ten or more waking hours [26–28], where non-wear time is set at 60 min of zero counts of which up to 2 min may be within the 0–100 count range [28, 29]. Current research points towards avoiding the use of direct monitor outputs such as energy expenditure estimations due to issues with reliability [21, 30]. Consensus points towards the use of both sedentary and moderate to vigorous physical activity (MVPA) cutoff points where sedentary activity is seen as 0 to > 100 counts per min [27, 29, 31, 32] and MVPA as > 1952 counts per min [29]. While the use of the LFE filter to calculate steps is not recommended, it may be applicable during data analysis of cutoff points for older adults [33, 34]. Future work on defining cutoff points in clinical populations will be considered.

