### Randomization

The randomization of subjects in study phase II is carried out by a study nurse after initial physical examination using an externally provided randomization list from the Friedrich-Alexander-Universität Erlangen-Nürnberg. Randomization is stratified based on the four prognostic dichotomous variables sex (male vs. female), progression of COPD (GOLD stages 1–2 vs. stages 3–4), age (<60 years vs. ≥ 60 years), and type of rehabilitation (PR in patients with stable COPD vs. PR after hospitalization due to subsequent COPD-related airway obstruction). The randomization list is created in blocks with six subjects per block. The study nurse is aware of the allocation in the different strata. The randomization scheme was generated by using the website Randomization.com.

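### The four stratification factors are called prognostic, but the primary ANCOVA as described names none of them; adding them costs almost nothing and may gain some precision.

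*Protocol article*

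**What the plan says.** Protocol article, Randomization: "Randomization is stratified based on the four prognostic dichotomous variables sex (male vs. female), progression of COPD" (GOLD 1–2 vs 3–4), age (under 60 vs 60 and over) and type of rehabilitation (stable COPD vs after hospitalization). That makes 2 × 2 × 2 × 2 = 16 strata. On blocking: "The randomization list is created in blocks with six subjects per block".

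Protocol article, Statistical analysis and evaluation: the primary objective is addressed by "a baseline-controlled comparison (covariance) of the post values between the initial assigned control and the intervention treatment group (intention-to-treat analysis") at t3 and t4. Baseline is the one adjustment mentioned. The section neither lists the stratification factors nor says that they are left out.

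Protocol article, Sample size and power calculation: the trial is sized on an analysis of covariance at t4. "In comparison to standard PR we expect a small effect (*d* = 0.3) at t4", with "an alpha error level of 5%, and statistical power of 80" per cent, which "results in a required sample of at least 351 subjects with complete data". The stratification factors do not appear there either.

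**The concern.** Stratifying on a prognostic factor balances it between arms, and this reduces the true sampling variance of the arm difference. A model that omits the factor cannot see the reduction. It leaves the factor's contribution in the residual variance, so its standard error describes a less precise trial than the one that was run. Confidence intervals are then somewhat too wide, the test falls below its nominal 5%, and precision that the design has already secured is not used.

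Here the plan itself calls the factors prognostic and collects them for every randomized patient, yet the model it describes makes no visible use of them. How much this matters depends on what the factors explain once baseline PA is in the model.

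**Working it through.** **Inputs from the protocol article.** d = 0.3 at t4, alpha 5%, power 80%, 351 complete cases, 30% dropout, 502 recruited (251 per group), 16 strata, blocks of six. Sidedness is not stated; the two-sided calculation reproduces the article's figure, and a one-sided one would give about 276.

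**Reproducing the plan.** ANCOVA F-test with two groups and one covariate: f = d/2 = 0.15, noncentrality λ = f²N, degrees of freedom 1 and N − 3. At N = 351, λ = 0.0225 × 351 = 7.90 on 1 and 348 df, and power is 80.03%. This is the smallest N that reaches 80%. For dropout, 351/0.70 = 501.4, rounded up to 502. Both figures reproduce, and neither relies on the stratification factors.

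**Adding the four factors.** Let R² be the share of the variance left after baseline PA that the factors explain. The documents give no value, so 0 to 0.15 is assumed. With five covariates:

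- Power: λ = 0.0225 × 351/(1 − R²), on 1 and 351 − 7 = 344 df.
- Inflation of the standard error when the factors are omitted: 1/√(1 − R²) − 1.
- Size of the test without them, assuming perfect balance: 2 × [1 − Φ(1.96/√(1 − R²))].

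| R² (assumed) | λ | Power with factors | N for 80% | SE inflation if omitted | Size if omitted |
|---|---|---|---|---|---|
| 0 | 7.90 | 80.0% | 351 | 0% | 5.0% |
| 0.02 | 8.06 | 80.8% | 344 | 1.0% | 4.8% |
| 0.05 | 8.31 | 82.0% | 334 | 2.6% | 4.4% |
| 0.10 | 8.78 | 84.0% | 316 | 5.4% | 3.9% |
| 0.15 | 9.29 | 86.0% | 299 | 8.5% | 3.4% |

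At R² = 0 the four extra covariates cost nothing visible: power stays at 80.0%.

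**Simulating the design.** Balance is not perfect with 16 strata, blocks of six and only 351 of 502 analysed. Simulations of that design took dropout as random. In the detailed set (4,000 runs per scenario) the four factors contributed equally and had assumed prevalences of 50–60%; Monte Carlo error was about 0.3 points for size and 0.6 for power.

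- At R² = 0.05, size without the factors was 4.6–4.7%. Power was 80.1% without and 81.4% with them; the gain across repeats was 1.3–1.5 points.
- At R² = 0.10, size was 3.9–4.5%. Power was 80.1% and 82.7%; the gain was 2.6–3 points.
- At R² = 0.15, size was about 3.7% and the gain about 4.6 points.

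The simulated gain is smaller than the tabulated one mainly because the model without the factors still benefits a little from the balance, so its true power lies slightly above 80%.

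**Scale of d.** All this takes d = 0.3 relative to the SD remaining after baseline adjustment. If d refers to the raw SD, baseline PA alone already lifts power above 80% (89.9% if it explained 25% of the variance), and there is less left to gain.

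**The case against.** The strongest objection is that the article is silent rather than wrong. A reader might infer that the model adjusts for baseline PA alone. The text does not say so: it lists no complete covariate set and excludes nothing, and a covariate list is often left to an SAP, which is not shown here. This stands, so the point cannot be put as an error or a contradiction. What remains is that the article does state what the comparison is controlled for. In the same section it marks the missing-data strategy as still to be developed, but it does not mark the covariates as open. An analyst following the text would fit the model without the factors.

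A reader might also infer that planned power is lost or that the test is invalid. Neither follows. The 351 was obtained without the factors, simulated power without them is about 80% or higher, and the error is on the conservative side.

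Nor does prognostic mean prognostic given baseline PA. Baseline PA may already carry most of what sex, age, GOLD stage and rehabilitation type predict, in which case the gain is close to nil.

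Finally, one might argue that these factors predict who returns a monitor, so that adjustment makes missing-at-random more credible. The documents expect 30% dropout but say nothing about who drops out, and the factors could enter the imputation model in any case. That argument is not relied on.

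**Conclusion.** The point holds as a conditional matter of efficiency and clarity. The described primary model names none of the four factors on which the trial stratifies. If they explain 0 to 15% of the variance left after baseline PA (assumed), naming them gains 0 to about 5–6 power points at 351 complete cases: about 1 at 2%, 1.5–2 at 5% and 3–4 at 10%. It also brings a test whose size would otherwise lie between 5% and about 3.4–3.7% back to its nominal level. The mechanism is certain; its size in this trial is unknown and could be near zero. The stated 351 and 502 are correct on their own terms, and the stated power is met either way.

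**What to change.** State the primary model for t3 and for t4 as: PA at follow-up = arm + t0 PA + sex + GOLD stage group + age group + type of rehabilitation, with main effects only and the values used at randomization. Report the model without the four factors as a sensitivity analysis. Fix this before outcome data are seen, so that the covariate set is not a later choice.

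The cost is one sentence and 4 of 348 residual degrees of freedom. The data are already collected in order to randomize, and the sample size does not change.

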With regard to the second point, the use of pedometers ranks as one of the most effective intervention elements for PA promotion [8]. Pedometers offer various possibilities to design behavior-change strategies [9]. In particular, pedometers are of use for persons to monitor and record their daily PA. Self-monitoring of behavior has been proven to be one of the most effective behavior-change techniques (BCT) in clinical populations [10]. Furthermore, pedometers are suitable in support of other BCT [11], e.g., individual goal setting in the unit steps per day or giving feedback on behavior. In nonclinical populations, pedometer-based interventions achieve an average increased PA level of approximately 2000 steps per day (effect size *d* = 0.68) in comparison to control groups [12]. Clinical populations provide preliminary evidence for the effectiveness of pedometers as part of rehabilitation for people with musculoskeletal disease [13], type-2 diabetes [14] as well as COPD [15, 16]. However, these results come from studies with small sample sizes in outpatient rehabilitation programs. Moreover, these studies often relate to short-term behavior changes during the rehabilitation period. The validity of most studies is further restricted by the usage of PA questionnaires instead of objective PA measurements [4]. Singh et al. [17] summarized that pedometer studies’ sample sizes in PR were not, up to this point, suitable for the detection of meaningful differences in PA levels. In the context of inpatient PR the potential of pedometers to first initiate and afterward maintain a physically active lifestyle in the long term has not yet been investigated.

The purpose of this paper is to describe the design of a randomized controlled trial (RCT) to (1) evaluate the effect of a short, pedometer-based behavior-change intervention (BCI) for inpatient PR in COPD patients with regard to the initiation (6-week follow-up) and maintenance (6-month follow-up) of a physically active lifestyle after PR and (2) to predict the expected intervention treatment effect and PA progression after PR discharge utilizing an innovative diagnostic battery that is based on the PARC model [7].

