The STAR study (Stay Active after Rehabilitation) aims to answer two central questions: does the integration of a pedometer-based intervention during inpatient PR for people with COPD, in comparison to standard PR, lead to a sustained improvement of PR results with regards to PA 6 weeks and 6 months after the PR? how does PA-related health competence of individuals with COPD develop during inpatient PR; and which individual PA-related health competence characteristics, in combination with which disease-specific prognostic assessments, enable the prediction of the expected intervention treatment effect as well as of the initiation and long-term maintenance of a physically active lifestyle after PR?

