#### Secondary hypothesis

The secondary outcomes (PA-related health competence of patients with COPD in combination with other PA behavior-related psychological measurements and disease-specific prognostic assessment) will enable the explanation of the treatment effect and the prediction of PA progression after PR discharge.

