Furthermore, the study generates a better understanding as to why patients with COPD manage or fail to initiate and maintain PA after PR. Based on the concepts from the model of PA-related health competence (PARC model) [7, 24] an adequate setup of individual physical and psychological determinants of PA will be assessed. The diagnostic battery will enrich our understanding of why the pedometer-based intervention works. In particular, the PA-related regulation competence is expected to contribute to this explanation of the intervention treatment effect. Furthermore, the results of a cluster-based analysis enable, regardless of the randomly controlled pedometer intervention’s effectiveness, the future identification of patients with COPD who will find it difficult to engage in long-term, health-promoting PA after PR. Acquiring a valid model for the prediction of PA behavior is the basis for optimizing intervention strategies to promote PA in the context of PR.

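### The secondary aim includes predicting and explaining the treatment effect, but the only analysis named for it, clusters linked over time, makes no comparison by arm

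*Protocol article*

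**What the plan says.** The aim is stated in several places. The purpose paragraph of the Background includes "to predict the expected intervention treatment effect and PA progression after PR discharge". The second of the two central questions, also in the Background, asks which competence characteristics, combined with disease-specific assessments, "enable the prediction of the expected intervention treatment effect", and also which predict the start and maintenance of an active lifestyle. Under Secondary hypothesis, the secondary outcomes "will enable the explanation of the treatment effect and the prediction of PA progression after PR discharge". The Discussion is more specific: "the PA-related regulation competence is expected to contribute to this explanation of the intervention treatment effect".

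The method is given under Statistical analysis and evaluation: "For the secondary objective a cluster-based analysis method will be used for longitudinal records", with LICUR as an example. There, "the analysis creates separate clusters for each measurement using the comprehensive assessment battery for t1 and t2", and accelerometer data are used for t0, t3 and t4. Then: "The second step of the cluster-based analysis links separately created clusters in a longitudinal way". The section names no other analysis for this objective.

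On size, Sample size and power calculation says: "The study sample size is adequate for the determination of PA predictors after rehabilitation". The only calculation in that section is for the primary comparison at t4.

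**The concern.** Predicting a treatment effect means asking whether the difference between intervention and control varies with something measured before the intervention. Explaining it means asking whether a change produced by the intervention carries the effect. Both questions need treatment arm in the analysis, and the named procedure gives arm no role. It groups patients by their profiles at each time point and follows the groups.

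The risk lies in the reporting. An association between cluster membership and later PA could be presented as a predictor of response to the pedometer intervention when it is only prognostic, meaning it would be seen equally in both arms. For clusters formed at t2, it could also be partly a consequence of treatment.

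**Working it through.** **1. Aim against method**

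| Component of the secondary aim | What it needs | Served by linked clusters as written? |
|---|---|---|
| Development of competence during rehabilitation | t1 and t2 profiles | Yes, descriptively |
| Prediction of PA at 6 weeks and 6 months | Earlier profiles related to t3 and t4 PA | Plausibly |
| Prediction of the treatment effect | Arm by pre-intervention characteristic | No: arm absent |
| Explanation of the treatment effect | Arm to change in competence to PA | No: arm absent |

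The Discussion supports this division. It describes the cluster results as useful for identifying patients who will struggle to stay active whether or not the intervention works, which is a prognostic use.

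**2. Timing.** Under Intervention arm, the two lessons fall at the end of week 2 and in the middle of week 3. Under Study flow and recruitment procedures, t1 is the initial assessment, before the lessons, and t2 is at the end of rehabilitation, after both. A t2 profile can therefore already reflect arm. It may serve as a prognostic factor or a mediator, but not as an effect modifier. Only t0 and t1 data can serve as modifiers.

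**3. The plan's own sample size.** Inputs from Sample size and power calculation: d = 0.3, alpha 5% (taken as two-sided), power 80%, 1:1 allocation, dropout 30%.

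- ANCOVA F test with f = d/2 = 0.15, numerator df 1 and one covariate: noncentrality = N f² = 351 × 0.0225 = 7.90, power 80.03%. N = 351 is the smallest N that reaches 80%, an exact match.
- Normal approximation: 2 × (1.960 + 0.842)² / 0.3² gives 175 per arm, or 350 in total, which agrees.
- Dropout: 351 / 0.70 = 501.4, rounded up to 502, a match.

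The stated figures are right for the main effect.

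**4. What 351 completers give for effect modification.** The documents give no figure, so the following are assumptions: a binary baseline modifier with share q, an interaction D (difference in treatment effect between the two subgroups) of 0.3 SD, two-sided 5%, and the normal approximation.

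- SE = √[4/(351q) + 4/(351(1−q))]
- Power = Φ(D/SE − 1.960)
- Smallest D detectable with 80% power = 2.802 × SE
- Completers for 80% power = 2.802² × [4/q + 4/(1−q)] / D²

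| Modifier split | SE | Power at D = 0.3 | Detectable D at 80% | Completers for 80% at D = 0.3 |
|---|---|---|---|---|
| 50/50 | 0.213 | 29% | 0.60 | about 1,396 |
| 30/70 | 0.233 | 25% | 0.65 | about 1,662 |
| 20/80 | 0.267 | 20% | 0.75 | about 2,181 |

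If baseline PA correlates r with follow-up PA, the SE shrinks by √(1−r²). For a 50/50 modifier, r = 0.3 gives 31% power (about 1,270 completers needed for 80%) and r = 0.7 gives 50% (about 712 needed).

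**The case against.** The strongest reply is that this is a condensed article. LICUR is given only as an example, and interaction or mediation models for a secondary aim are ordinary content for an analysis plan that is not shown. Clusters are formed per time point, so t1 clusters could later be crossed with arm. All of that is fair. It limits the point to the method as written and rules out saying that no extension of it could work. It does not remove the point, because the article assigns a class of method to the whole objective and that class does not address two of its components.

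A reader might also draw stronger conclusions that the documents do not support:

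- **That the second central question cannot be answered at all.** Competence development and prediction of later PA are part of that question, and longitudinal clustering can plausibly serve them.
- **That the adequacy sentence is shown to be false.** It speaks of predictors of PA, not of the treatment effect. It comes without a calculation, but nothing in the documents shows that 351 is too few for a prognostic model.
- **That using t2 data is an error.** The text never says t2 clusters will be modifiers. They are legitimate for describing development, for prognosis and for explanation.
- **That patients are lost because the method's name mentions removing a residue.** The article does not say who would form the residue or how they would be handled, so nothing can be built on it.

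**Conclusion.** The point holds as a mismatch between aim and method. For the treatment-effect part of the secondary aim, the article names an analysis that makes no comparison by arm. It therefore cannot show whether the effect varies with a patient characteristic or is carried by a change in competence.

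The power figures are secondary to this and depend on their assumptions. Taken together, the range is about 20% to 50% for an interaction as large as the assumed main effect. The figures describe a binary modifier, whereas continuous scores are preferable, so they indicate scale only and should not be quoted as the trial's power. They do support labelling any effect-modification analysis as exploratory.

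The primary comparison and its sample size are unaffected. This is a cheap improvement.

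**What to change.** 1. **Clustering.** Keep it, labelled as descriptive and prognostic.
2. **Prediction of the treatment effect.** Add arm-by-characteristic terms to the primary baseline-adjusted model for a short prespecified list measured before the intervention lessons (t0 and t1 only), kept continuous where possible. Report them as exploratory, with confidence intervals.
3. **Explanation of the treatment effect.** Use the t1-to-t2 change in PARC scores as a mediator. State that t2 clusters will not be used as effect modifiers.
4. **Sample size text.** Say that the adequacy sentence refers to prognostic predictors of PA and that the 351-completer calculation covers the main effect only. If interaction power is mentioned, give the range with its assumptions.

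The cost is some wording and modest extra analysis of data already being collected. The downside is a less favourable statement of what the secondary aim can deliver.
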